### Implementation

A member of the research team will instruct the patients, their families and the ward staff in the use of the CPAP. The ward staff will introduce, apply and adjust the mask for comfort, until the participants are satisfied. The research staff will also review the subjects each morning to identify any barriers to use and address any difficulties. The feasibility study suggested that CPAP adherence could be maximized through early and careful attention to any difficulties.

### Treatment duration

In the able-bodied with OSA, a minimum of 6 weeks of treatment is required to establish CPAP adherence and to observe changes in neuropsychological functioning outcomes. Three months of therapy has been demonstrated as sufficient to improve neurocognitive functioning, specifically improved memory, in the able-bodied with OSA
[29]. Other cardiovascular changes occur more slowly; however, improvements would be evident after three months of therapy. We propose to treat people for three months or until hospital discharge.

### Data analysis

All analyses will be performed on an intention-to-treat basis. This presents particular challenges in a clinical trial, such as this, where effective clinician and patient blinding of treatment allocation is impossible.

### Blinding of assessments

In a trial of a physical device such as this, patient and clinical blinding is impossible. We therefore propose to perform blinded assessment of the maximum proportion of the outcome measures. The following measures will be blinded to group allocation:

1. All initial, baseline data, including PSG staging and scoring.

2. Cognitive test battery.

3. Spirometry.

4. Quality of life and sleep questionnaires.

The clinical scenarios outlined below will be managed as described. Both of the first two scenarios occurred during the feasibility trial.

#### Unable to continue with CPAP

Any participant who chooses to cease CPAP treatment will remain in the study for 3 months. The test collection battery will proceed as planned.

#### Hospital discharge prior to end of treatment period

To continue the proposed randomized controlled trial in the home is beyond the scope of the study, therefore the treatment period will cease at hospital discharge. The end study data collection battery will be performed in the week prior to discharge and all obtained results will be treated as ‘last observation carried forward’.

#### Randomized group cross-over

Patients with OSA who are randomized to usual care but then proceed to be treated with CPAP or noninvasive ventilatory support will remain in their allocated group for primary analysis purposes.

### Trial data management

Each site will be responsible for local storage of hard-copy data, which will be entered online into a centralized database. Automated, digital data capture methods will be used wherever possible. Sleep studies will be performed locally and data transferred electronically to the coordinating centre for analysis. This process has been successfully used by the research team in a previous interlaboratory concordance trial
[30].

### Estimated subject numbers

This is a three-month treatment trial at a time where there is profound disruption in the life of the study participants. Over this acute period, direct measurements of quality of life and performance in rehabilitation will not demonstrate the efficacy or otherwise of CPAP. The feasibility study clearly demonstrated that there was substantial variability in quality of life post injury, unrelated to OSA or CPAP, thus rendering these outcomes unsuitable for demonstrating short-term improvement in a study sample of constrained size. We are, therefore, basing our sample size calculations on neurocognitive performance, a number of measures of which form our test battery. The specific neurocognitive test in the test battery, which is best characterized in both the spinal population and OSA, is the PASAT. Lower (worse) PASAT scores correlate with sleep fragmentation severity in the able-bodied
[31] and OSA severity in quadriplegia
[15]. Lower PASAT scores are also associated with diminished frontal lobe function, as assessed by functional magnetic resonance imaging
[32] and a mean difference in PASAT scores of seven discriminates between those with and without cognitive impairment in multiple sclerosis
[33]. In the able-bodied with OSA, those adherent to CPAP over three months have a PASAT score 18 units higher than those who are not (standard deviation of 33)
[34].

Assuming a mean difference between the study arms of 18
[34], a standard deviation of 33, a power of 0.8, an *α* value of 0.05 and a nonadherence to CPAP rate of 15%, 150 subjects will be randomized. To ensure that 150 participants complete the study, we estimate that approximately 820 admissions with quadriplegia will be required across our collaborating centres (at least 8 of 44 admissions will meet the inclusion criteria, fail to meet the exclusion criteria, agree to participate, have OSA and tolerate CPAP). This sample is also adequate to detect any true difference between secondary outcomes, such as sleepiness (KSS number required = 44).

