The specific aim of the COSAQ study is to determine the effect of nocturnal auto-titrating CPAP treatment on neuropsychological function, quality of life, autonomic dysfunction and breathing in people with acute quadriplegia and OSA. To address this aim, one primary and two secondary hypotheses were developed and will be tested. The primary hypothesis is that usual care and nocturnal CPAP treatment will improve neuropsychological functioning more than will usual care alone; specifically, working memory as tested on the Paced Auditory Serial Addition Test (PASAT). The first secondary hypothesis is that the magnitude of improvement in neuropsychological function will be predicted by the severity of baseline sleepiness (Karolinska Sleepiness Scale (KSS)), sleep fragmentation (Sleep Efficiency, Arousal Index) and sleep apnoea (apnoea hypopnoea index (AHI), percentage total sleep time with SpO_2_ < 90%). The second secondary hypothesis is that usual care and nocturnal CPAP will improve the following parameters more than usual care alone:

1. Sleepiness and symptoms: Karolinska Sleepiness Scale (KSS) and the Basic Nordic Sleep Questionnaire (BNSQ).

2. Lung Function: spirometry.

3. Quality of life: Assessment of Quality of Life (AQoL).

4. Autonomic dysfunction: event diary and heart rate variability.

5. Health utility: AQoL-derived change in utility and associated quality-adjusted life years (QALY).

6. Depression and anxiety: Hospital Anxiety and Depression Scale (HADS) and the Profile of Mood States (POMS).

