## Trial status

The trial commenced recruitment in July 2009. Recruitment will cease when 150 trial participants have been randomized. It is anticipated that this target will be reached by mid-2015.

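### The protocol says 150 participants can detect every real difference in the secondary outcomes; no fixed sample can, and the same section doubts quality of life at this size

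*Protocol article*

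**What the plan says.** The section Estimated subject numbers makes two statements about what the sample can show beyond the primary outcome.

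It first explains why the trial is not powered on quality of life. The feasibility study found large variation after injury that had nothing to do with sleep apnoea or CPAP, "thus rendering these outcomes unsuitable for demonstrating short-term improvement in a study sample of constrained size". The trial is therefore sized on the PASAT.

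The section then ends: "This sample is also adequate to detect any true difference between secondary outcomes, such as sleepiness (KSS number required = 44"). The KSS is offered as an example of a general claim about the secondary outcomes.

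The Background, under the second secondary hypothesis, includes "Quality of life: Assessment of Quality of Life (AQoL"), and separately AQoL-derived utility and QALYs. The other items are the BNSQ alongside the KSS, spirometry, autonomic dysfunction, HADS and POMS. For each, the hypothesis is that CPAP plus usual care improves the outcome more than usual care alone.

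**The concern.** A sample of fixed size has adequate power only above some effect size; below it, real differences are more likely to be missed. A statement that the sample suffices for every real difference is therefore wrong whatever the outcome, the variance or the method of analysis.

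The sentence also cannot stand beside the earlier one. If quality of life is too variable to show improvement in a sample of this kind, the sample is not adequate for every secondary outcome, because AQoL is one of them.

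What is at stake is the reading of null results. If the sample were able to detect any real difference, a non-significant secondary result would mean that there is none. The design cannot support that inference for small or moderate effects on mood, lung function, sleep symptoms or quality of life.

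**Working it through.** **Inputs from Estimated subject numbers.** The target PASAT difference is 18 units, with an SD of 33; alpha is 5% and the required power 80%. An allowance is then made for poor use of the device: "a nonadherence to CPAP rate of 15%, 150 subjects will be randomized". Trial status confirms the total: "Recruitment will cease when 150 trial participants have been randomized".

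**Assumptions.** The article gives neither the allocation ratio nor the sidedness of the test. I take 1:1 (75 per arm), two-sided, with all 150 contributing data.

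**1. Reproduce the plan's own figure.** If the 15% who are nonadherent gain nothing, the expected difference is 18 × 0.85 = 15.3.

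n per arm = 2 × (1.960 + 0.842)² × 33² / 15.3² = 2 × 7.849 × 1089 / 234.09 = 73.03, rounded up to 74, or 148 in total. That matches 150 closely; power at 150 is about 81%. Inflating the undiluted sample size by 1/0.85² gives about 147 (149 from the t distribution), which also agrees. A one-sided test does not reproduce it (116 in total with the diluted effect). The assumptions are therefore consistent with the plan, and the primary calculation stands.

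**2. Smallest difference with 80% power at 75 per arm, unadjusted.**

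d = (1.960 + 0.842) × √(2/75) = 2.802 × 0.1633 = 0.457; the t distribution gives 0.460. So about 0.46 SD.

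**3. Power for smaller true differences.** Power ≈ Φ(d × √(75/2) − 1.960), with √37.5 = 6.124.

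| True difference (SD) | d × 6.124 − 1.960 | Power at 150 | Total needed for 80% power |
|---|---|---|---|
| 0.2 | −0.735 | 23% | 786 |
| 0.3 | −0.123 | 45% | 350 |
| 0.4 | 0.489 | 69% | 198 |
| 0.5 | 1.102 | 86% | 126 |

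**4. Effect of baseline adjustment.** With a correlation r between baseline and end-of-study values, the detectable difference is multiplied by √(1 − r²). The values of r are assumptions; the article gives none.

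- r = 0.5: 0.46 × √0.75 = 0.40 SD
- r = 0.7: 0.46 × √0.51 = 0.33 SD

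The limit moves down but does not vanish.

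**5. What the 44 for the KSS supports.** At an assumed 80% power and two-sided 5%, the implied standardised effect depends on what the 44 counts (t-based values):

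- 44 in total, 22 per arm: about 0.86 SD
- 44 per arm: about 0.60 SD
- 44 in a paired comparison: about 0.43 SD of the within-person change (normal approximation 2.802/√44 = 0.42)

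On any of these readings the figure concerns one outcome and one assumed effect. It says nothing about the difference or variability expected for AQoL, spirometry, HADS, POMS or autonomic events.

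**The case against.** The best defence is that this is one loosely worded sentence. Its only numerical content, that 44 is fewer than 150, is not shown to be wrong, and no sample size, endpoint or analysis depends on it. That is fair as to scale. But the sentence speaks of secondary outcomes in the plural and presents the KSS as an instance, so a reader cannot tell that only the KSS was considered.

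Several stronger readings are tempting, and the document does not support them.

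- **That the KSS figure is defective because its inputs are not given, or that it implies a very large effect.** An article may leave such inputs to the full protocol. The implied effect runs from about 0.43 to 0.86 SD depending on a design the article does not state.
- **That 0.46 SD is a hard floor for the secondary outcomes.** Statistical analyses provides for repeated measures analysis of variance and mixed models; the KSS is measured weekly and spirometry monthly. These may lower the limit, as step 4 shows for baseline adjustment. A limit in SD units also does not fit autonomic dysreflexia, which is analysed as a rate.
- **That listing AQoL as a secondary outcome is itself an error.** A trial may include a weakly powered secondary outcome. The conflict arises only with the claim of general adequacy. The section names quality of life and rehabilitation performance, not AQoL or utility; the link to AQoL is direct, because it is the trial's quality of life instrument, while the link to utility is an inference from its derivation.
- **That the trial intends to read non-significance as no effect.** Nothing says so, and for quality of life the section warns that such measures will not settle efficacy either way. The risk comes from the adequacy sentence if taken at face value.

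**Conclusion.** The concern holds for the general adequacy claim. The sample is credited with a power property it does not have, and the claim conflicts with the same section's view of quality of life, given that AQoL is a listed secondary outcome. With 75 per arm, two-sided 5% and an unadjusted comparison of means, 80% power is reached at about 0.46 SD, and a true difference of 0.3 SD would be missed more often than found. Under baseline adjustment the limit is about 0.40 SD at r = 0.5 or 0.33 SD at r = 0.7. Allocation, sidedness, complete data and these correlations are my assumptions; the conclusion that some real differences will go undetected needs none of them.

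A reader might infer that the total of 150 is in doubt. It is not: the primary calculation reproduces at 148. This is a correction to a stated capability, worth making because it governs how null secondary results are read.

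**What to change.** Limit the adequacy claim to the KSS, and replace the general claim with wording such as:

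> For continuous secondary outcomes, 150 participants (assuming 75 per arm, two-sided 5%, unadjusted comparison of means) give 80% power for between-arm differences of about 0.46 SD; baseline-adjusted or repeated-measures analysis may lower this (about 0.40 SD at an assumed correlation of 0.5, 0.33 SD at 0.7). Smaller effects, including on AQoL, cannot be excluded. Secondary results will be reported as estimates with 95% confidence intervals, and non-significance will not be read as no effect.

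This also removes the conflict with the earlier remark on quality of life, and AQoL can stay as a secondary outcome. Restricting the statement to continuous outcomes keeps it from being applied to autonomic event rates.

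The cost is a few lines of text and a less favourable stated capability. The sample size, the outcomes and the analyses do not change.

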### Adherence with therapy

All usage data collected by the treatment devices will be downloaded weekly and analyzed fully. Based on previous research in the able-bodied population with OSA, improvements in memory, sleepiness and daily function may be observed if CPAP is used for 4 hours per night for five days out of every seven
[35,36]. Those subjects who use CPAP for at least this amount will be classified as ‘adherent’ for each week of the study

### Statistical analyses

Usage data from the CPAP devices will be described and subjects classified as adherent, as described. The proportion of subjects continuing to use CPAP over the three months of treatment will be plotted and examined using survival (Kaplan-Meier) analysis. Statistics describing the distribution of CPAP usage, average numbers of hours used per night, and so on, will be calculated.

Changes in neurocognitive performance, AQoL, BNSQ and KSS will be examined with paired *t* tests, repeated measures analysis of variance and generalized linear mixed models, as appropriate. The rate of autonomic dysreflexia and the time course of development will be compared with *χ* squared and mixed model regression modelling as appropriate. Exploratory linear and logistic regression modelling will be performed to determine whether the average number of hours used or the likelihood of adherence can be predicted by any of the groups’ baseline characteristics.

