**Methods/design:**

Specialist spinal cord injury centres across Australia, New Zealand, the UK and Canada will recruit medically stable individuals who have sustained a (new) traumatic quadriplegia (complete or incomplete second cervical to first thoracic level lesions). Participants will be screened for obstructive sleep apnoea using full, portable sleep studies. Those with an apnoea hypopnoea index greater than 10 per hour will proceed to an initial three-night trial of CPAP. Those who can tolerate CPAP for at least 4 hours on at least one night of the initial trial will be randomized to either usual care or a 3-month period of auto-titrating CPAP. The primary hypothesis is that nocturnal CPAP will improve neuropsychological functioning more than usual care alone. The secondary hypothesis is that the magnitude of improvement of neuropsychological function will be predicted by the severity of baseline sleepiness measures, sleep fragmentation and sleep apnoea. Neuropsychological tests and full polysomnography will be performed at baseline and 3 months with interim measures of sleepiness and symptoms of autonomic dysfunction measured weekly. Spirometry will be performed monthly. Neuropsychological tests will be administered by blinded assessors. Recruitment commenced in July 2009.

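### Paired t tests are listed for the change in PASAT, but they compare each arm with its own baseline and cannot test the between-arm primary hypothesis; a baseline-adjusted between-arm comparison should be named as primary

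*Protocol article*

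**What the plan says.** All references are to the protocol article.

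- **Hypothesis (Background, final paragraphs).** "The primary hypothesis is that usual care and nocturnal CPAP treatment will improve neuropsychological functioning more than will usual care alone". The same sentence narrows this to working memory measured by PASAT. The contrast is between arms.
- **Sample size (Estimated subject numbers).** "Assuming a mean difference between the study arms of 18". With SD 33, power 0.8, alpha 0.05 and 15% nonadherence, the section arrives at 150 participants. This too is a between-arm quantity.
- **Timing (Abstract, Methods/design).** "Neuropsychological tests and full polysomnography will be performed at baseline and 3 months". PASAT therefore has two time points; End study data collection allows the second to fall at hospital discharge.
- **Analysis (Statistical analyses).** "Changes in neurocognitive performance, AQoL, BNSQ and KSS will be examined with paired *t* tests, repeated measures analysis of variance". The sentence adds mixed models as a third option and closes by leaving the choice to what is appropriate. It is the only sentence in the article on how PASAT will be analysed.

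**The concern.** A paired t test on PASAT asks whether one arm moved from its own starting value. It makes no use of the other arm or of randomization. The same oral test is given twice to recently injured people, so both arms may well improve through practice and recovery. A significant paired test with CPAP beside a non-significant one with usual care would then look like support for the hypothesis without being a test of it.

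The hypothesis and the sample size are both comparative, yet one of the methods listed for the primary outcome contains no comparison between arms. The methods that do contain one leave baseline PASAT unadjusted in their usual two-time-point form, although every participant has it measured before randomization. What is at stake is whether the primary conclusion rests on the randomized comparison, and how precise that comparison is.

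**Working it through.** **Inputs from the article:** difference 18, SD 33, power 0.8, alpha 0.05, nonadherence 15%, 150 randomized.

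**Assumptions, because the article does not state them:** two-sided test; 1:1 allocation (75 per arm); 33 read as the SD of the score; pre-post correlation ρ and any gain common to both arms, shown as ranges.

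**1. Which comparison gives 150?** For two independent means, n per arm = 2(1.960 + 0.842)² × SD² / difference².
- Difference 18: 2 × 7.85 × 1089 / 324 ≈ 52.8, so 53 per arm and 106 in total. Dividing by 0.85 gives 125, which is not 150.
- Difference diluted by nonadherence, 18 × 0.85 = 15.3: 2 × 7.85 × 1089 / 234.1 ≈ 73.0. Rounding with the t correction gives 74 per arm, 148 in total, close to 150.
- Power at 75 per arm: SE = 33 × √(2/75) = 5.39; 15.3 / 5.39 = 2.84; Φ(2.84 − 1.96) = 0.81.

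The stated number is thus reproduced as a two-arm comparison of means.

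**2. What can paired tests show when CPAP has no effect?** Let both arms gain g points. The SD of change is 33√(2(1 − ρ)), and each paired test has noncentrality g√75 / SD of change. For example, with ρ = 0.5 the SD of change is 33, and g = 5 gives 5 × 8.66 / 33 = 1.31 and a 25% chance of significance. The arms are independent, so the chance of a significant gain with CPAP and no significance with usual care is about p(1 − p).

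| ρ | Common gain | Paired test significant in the CPAP arm | CPAP significant, usual care not |
|---|---|---|---|
| 0.5 | 5 | 25% | 19% |
| 0.5 | 7 | 44% | 25% |
| 0.7 | 5 | 39% | 24% |
| 0.7 | 7 | 65% | 23% |
| 0.8 | 5 | 54% | 25% |
| 0.8 | 7 | 82% | 15% |

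A two-sided 5% between-arm test would wrongly favour CPAP in 2.5% of trials. The pattern depends on the common gain. With no gain it occurs in 2.4%. With a gain of 12 it occurs in 11% at ρ = 0.5 and in 0.2% at ρ = 0.8, because both arms then tend to be significant.

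**3. What do the valid options give at 150?** With two time points and complete data, the group-by-time term is the two-sample test of change, with SD 33√(2(1 − ρ)). ANCOVA has residual SD 33√(1 − ρ²). The ratio of variances, ANCOVA to change score, is (1 − ρ²) / (2(1 − ρ)) = (1 + ρ)/2, which never exceeds 1. Power for a difference of 15.3 with 75 per arm:

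| ρ | Change score (group-by-time) | ANCOVA |
|---|---|---|
| 0 | 0.52 | 0.81 |
| 0.3 | 0.67 | 0.85 |
| 0.5 | 0.81 | 0.91 |
| 0.7 | 0.96 | 0.98 |
| 0.8 | 0.99 | >0.99 |

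The change-score test reaches the planned power only if ρ is about 0.5 or more. ANCOVA reaches it at every ρ shown.

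**The case against.** The between-arm intent is clear elsewhere: in the hypothesis, in the sample size, in the intention-to-treat statement, and in the rule under Randomized group cross-over that participants stay in their allocated group for the primary analysis. Two of the three listed methods can test the hypothesis. The sentence covers outcomes with different schedules (KSS weekly, cognitive tests twice), so its closing qualifier may only mean that the method will be matched to the outcome. An article may also leave the exact primary model and its covariates to a fuller document. All of this stands. The absence of a named model is therefore not the point here; the listing of a test that cannot answer the question is.

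Four stronger readings are tempting, and the article does not support them:

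- **That paired t tests are the primary analysis, or that efficacy will be claimed from one significant arm.** The article states no such rule, and order in a list is not priority.
- **That choosing among the methods raises type I error to about 10%.** That figure takes the best of several tests, including a post-score t test and ANCOVA, which the article does not name. The group-by-time test alone keeps about 5%.
- **That adjustment lifts power from about 0.81 whatever the correlation.** That comparator is an unadjusted post-score test, which is not listed. Against the listed change-score equivalent, the gain is about 0.10 at ρ = 0.5 and 0.02 at ρ = 0.7.
- **That 150 is too few.** It is reproduced, and it suffices for ANCOVA.

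**Conclusion.** The point holds in limited form. A within-arm test is listed for an outcome whose hypothesis and sample size are between-arm, and it cannot serve that purpose. Used for inference, it could mislead in about 15 to 25% of trials with no CPAP effect, provided that both arms gain 5 to 7 points and the correlation lies between 0.5 and 0.8. Neither figure is in the article, and with no common gain the excess disappears. The remaining listed methods are valid through group-by-time but, as an unadjusted change-score comparison, never have more power than ANCOVA. How much is gained depends on the unknown correlation: substantial when it is low, small at 0.7 and above. This is a correction of analysis wording, not a flaw in the design or the sample size.

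**What to change.** Under Statistical analyses, give PASAT its own sentence, for example: *The primary analysis is an intention-to-treat comparison between randomized arms of end-study PASAT by ANCOVA, with arm and baseline PASAT in the model, at a two-sided 5% level, reported as an adjusted mean difference with 95% confidence interval.* An equivalent baseline-adjusted mixed model would serve as well. State that paired t tests describe change within arms only and are not used to compare treatments.

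The cost is a few lines of text, to be settled before unblinded data are seen. Baseline PASAT is already collected, so no new data or participants are needed, and the target of 150 stays as it is.
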